**Significance**

Following the pilot RCT and PhD, I plan to conduct a fully powered, community-based RCT to determine the effectiveness and cost-effectiveness of this intervention in reducing the need for paediatrician services and improving child and parent outcomes.

In the long term, the FindWays website is potentially significant because: i) it may help families improve their child behaviour and emotions at home, or ii) find and engage with available evidence-based services earlier.

If this DHI can link some families to the right treatments, without seeing a paediatrician, it will increase the efficiency of the health system. With fewer families on waitlists, children with more complex or severe problems may be seen sooner. The overall capacity of the health system may be increased as we expect families to access group parenting programs, and scalable online programs, where there is greater capacity to see more children than through individual face to face appointments with a specialist.

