**Long term risks**

One theoretical long-term risk exists from using the platform, which is whether parents feel they find the help they need from the website and linking them to alternative services, so they don’t proceed to see the paediatrician. It is worth noting that this attrition is common among paediatrician waitlists, and may represent the families finding alternative services or a resolution of the problems they were referred for. To reduce the risk of parents prematurely withdrawing from the waitlist, the website is framed around encouraging parents to always access the paediatrician, and the strategies and services provided within the website focus on giving parents strategies and services to try while they wait for an appointment with the paediatrician.

It is also worth noting a similar mental health service navigation website for teenagers found no adverse effects from their intervention in either their feasibility or efficacy trial.^14,15^

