**Table 1. Study Objectives, data sources, measures, data collection time points and outcomes**

| Primary and Secondary Objectives | Data Sources | Methods of collection | Data Collection Timepoints | Outcomes of Interest |
| --- | --- | --- | --- | --- |
| Acceptability – task completion | Parent Survey | online via REDCap | Baseline and 4 months | Whether parents accessed any of the resources within the website, and whether this changed the parent’s behaviour (eg help-seeking, implementing new strategies) |
| Acceptability - recruitment | Clinic database | Print copy of database | recorded at weekly intervals for the duration of recruitment | How many eligible patients were flagged by the paediatrician, how many were contacted by the clinic, and how many agreed to pass on their details to me and how many were randomised to the intervention/control. |
| Acceptability – retention and usage | Google Analytics | Manual data extraction from Google Analytics | Baseline and Weekly intervals for 4 months | Number of page views, individual sessions, time spent on each page.  Strategies viewed, provider profiles viewed, programs viewed. |
| Acceptability - recommendation | Parent Survey | online via REDCap | 4 months | Likert scale of NET recommender score from 0-10. |
| Acceptability – usability and safety | Qualitative Interview | Qualitative interview with parents over 20 minutes | 4 months | Understand the parent’s experience using the platform, barriers to use and any perceived adverse outcomes |
| Secondary outcome: Child Behaviour and emotions | Parent Survey | Control and website group surveys completed online via REDCap. | Baseline and 4 months | Strengths and Difficulties Questionnaire* (SDQ) measuring changes in behaviour and impact |
| Family impact of child’s behaviour and emotions | Parent survey | Control and website group surveys completed online via REDCap. | Baseline and 4 months | SDQ impact statement* measuring the impact of the child’s behaviour and emotions on their functioning and the family. |
| Secondary outcome: Parent mental health / distress | Parent Survey | Control and website group surveys completed online via REDCap. | Baseline and 4 months | Depression, Anxiety and Stress Scale* (DASS-21) measuring changes in parents’ symptoms |

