# Trial population

The trial population will be all eligible parents of children, aged two-12 years. with a behavioural and/or emotional problem, who are referred to a paediatric clinic for their first review. These paediatric clinics will be either Geelong Children’s Clinic, Geelong Paediatric Group or Barwon Paediatrics. The referred child can either be accepted or declined by the clinic.

We expect to recruit at least 20 parents every month for three months. This estimate is based on the high number of monthly referrals for behavioural or emotional problems in 2-12 year old to these clinics (estimated to be 20 referrals every week across the 3 clinics). Further, the number of accepted referrals who were recruited within [name]’s qualitative study (HREC 2019.160), was 5 parents per week at each study site.

No power calculation has been done as the trial is not intended to assess the effectiveness of the intervention. Typically, acceptability and feasibility trials recruit around 20 participants, though 60 will give us a stronger indication of difference in acceptability between the intervention groups, and a larger number of eligible participants for the qualitative component of the study, which ideally requires around 20 participants to reach data saturation.

Exclusion criteria are listed in the table below. These criteria are justified because: i) children with a diagnosed intellectual disability or autism spectrum disorder require specialised treatments that are not listed within the platform; ii) children in out of home care are especially vulnerable and again require specialised programs with an emphasis on attachment and trauma; iii) any child requiring an urgent review (eg high severity or possibility of medical cause) is less likely to gain benefit from the website due to the shorter time frame waiting for a paediatrician review, and may be less likely to benefit from the programs and interventions listed in the website because of the increased severity.

Parents are the sole focus of the intervention, and the only source of outcome data. Children are not directed to use the website or participate in the collection of any measures. Only one parent will be consented for each child referred to the clinic.

**Table 2**. Inclusion and exclusion criteria

| *Inclusion criteria* | *Exclusion criteria* |
| --- | --- |

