# Schedule of assessments

Table 3. Sequence of enrolment, consent and measures

|  | **TRIAL PERIOD** | | | |
| --- | --- | --- | --- | --- |
|  | **Enrolment** | **Allocation to intervention** | **Post allocation** | **Close-out** |
| **TIME POINT**** | ***-t_1_*** | **0** | ***t_1_*** | ***t_x_*** |
| **ENROLMENT:** |  |  |  |  |
| **Eligibility screen** | X |  |  |  |
| **Informed consent** | X |  |  |  |
| **Allocation to intervention** |  | X |  |  |
| **INTERVENTIONS:** |  |  |  |  |
| ***Website group*** |  |  |  |  |
| ***Control group*** |  |  |  |  |
| **ASSESSMENTS:** |  |  |  |  |
| ***Child behaviour, parent mental health survey*** | X |  |  | X |
| ***Demographics survey*** | X |  |  |  |
| ***DHI usage as measured by Google Analytics*** |  |  | X  (continuous) | X |
| ***Acceptability survey (FindWays group only)*** |  |  |  | X |
| ***Qualitative interview (Optional consent from FindWays group only)*** |  |  |  | X  (optional) |
| ***Health service use survey*** | X |  |  | X |

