For parents in the Website group, they will be contacted via SMS to participate in a telephone semi-structured interview. [name] will conduct all the phone interviews as per the interview guide. The interview will last approximately 30 minutes. [name] has conducted qualitative interviews before (HREC 2019.160), attended qualitative methods training through University of Melbourne courses with [name] and attending workshops as part of his PhD Mental Health Program. This interview is designed to better understand the parent’s experience using the platform, including understanding any adverse events (including rare safety issues) that occurred because of using the FindWays website.

We will request permission to audio record the interviews from caregivers. The interview will be recorded on [name] digital dictaphone whilst conducting the interview on speaker phone in a walled office at MCRI or at [name] home office. If the respondent does not consent to an audio recording of the interview, [name] will take notes during the interview, and use these written notes for data analysis. All audio recordings will be transcribed verbatim by either [name] or Outscribe. Outscribe is an on-demand transcription Australian based service, used previously by researchers at MCRI. The information in the interview will be related to the use of the platform, and not asking about sensitive health information.

Audio recordings will be retained after transcription for 5 years. They will be stored on a MCRI network restricted access folder on a password protected computer. Audio recordings are required to be stored as the source data of the qualitative interviews to ensure an audit trail is maintained.

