Four months after starting the intervention, the parents in the Website group who gave optional consent to participate in a semi-structured interview of 30 minutes, will be contacted (see interview guide). Completion of this qualitative survey poses 3 possible ethical complications: (i) the parent becomes distressed during the phone interview, (ii) parent’s description of them using the FindWays website indicates need for urgent intervention (eg perhaps because the child’s situation has deteriorated over the past 4 months); or (iii) parent may say something about using the website that raises concerns about child’s safety and welfare (eg a protective concern).

While unlikely, it’s possible that participant distress may arise as parent’s talk about their experience using the platform. There is a small possibility that this may be uncomfortable, upsetting and frustrating. In this research setting, there are additional methods available to prevent and manage the potential for parental distress. Specifically, the parents can stop the interview at any time, they can avoid answering any questions they don’t want to, and that it is OK if they choose to do so.

If any parents become distressed during the phone interview, we will adhere to the following initial procedure:

1. acknowledge they are upset
2. talk to them empathetically and listen to their concerns
3. give them the opportunity for a break or withdraw from the study

If this is unsuccessful, and the participant becomes more distressed, we will escalate the procedure to:

1. Terminate using the interview guide;
2. [name] will attempt to calm the participant and direct them towards appropriate, available resources, depending on their cause of distress; These resources include
   1. Asking about support persons specific to that person (eg family, friends) who they can discuss their concerns with.
   2. The GP who made their referral
   3. Mental health resources – national help lines (Parentline [name]) or online self-help resources (Raising children network, Beyond Blue)
   4. Ask if we may call them in a couple of days to check in on how they are going, where Investigator ([name]) will contact the caregiver to debrief and counsel as appropriate.
   5. Ask them if they would like [name] to call an external agency on their behalf.

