# Reporting of safety events

Although it is not expected that this intervention poses a risk of a serious adverse event, if there is a SAE, this is how it will be reported.

Any SAE occurring in a study participant will be reported to the HREC within 24-72 hours of occurrence, in accordance with the safety reporting policy of the HREC. The HREC safety reporting form will be completed, signed and submitted by an investigator.

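### Parent-perceived harms are asked about only in an optional Website-arm interview, and leaving the paediatrician waitlist is recorded in neither arm, so the pilot can compare neither between arms

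*Protocol*

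**What the plan says.** Table 1 (section 3.1) has one row that names safety. Its source is the qualitative interview at 4 months, and its content includes "barriers to use and any perceived adverse outcomes". Table 3 (section 7.2) lists that interview as "Qualitative interview (Optional consent from FindWays group only". Section 8 (Participant distress) again limits it to "the parents in the Website group who gave optional consent to participate in a semi-structured interview". Section 7.3 gives its purpose as exploring the parent's experience, "including understanding any adverse events (including rare safety issues) that occurred because of using the FindWays website". Website parents who withdraw are also invited (section 7.3.1). No equivalent contact is described for control parents.

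Section 2.3.1 (Long term risks) describes a theoretical risk that parents find help through the website and do not go on to the paediatrician. It says such attrition is common in any case and may mean that other help was found or that the problem resolved. The response, introduced by "To reduce the risk of parents prematurely withdrawing from the waitlist", lies in how the website is framed. Section 2.2 (Significance) presents treatment without a paediatrician as an efficiency gain, and the planned full RCT is to study "reducing the need for paediatrician services and improving child and parent outcomes".

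Section 8.1 states: "Any SAE occurring in a study participant will be reported to the HREC within 24-72 hours of occurrence", in line with the HREC's own safety reporting policy. Section 4.2 states: "Parents are the sole focus of the intervention, and the only source of outcome data".

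**The concern.** An event that is common without the website can show an excess, or a benefit, only against the control arm. The protocol gives the event two opposite readings and lists no measurement of it in either arm. Perceived harms are asked about in one arm only, among parents who agree to a further interview. A report that no harm was mentioned would have no comparator and would rest on a self-selected group.

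The second consequence is for the next trial. The primary objective includes the feasibility of the study design and measures before a full RCT. If that RCT is to examine the need for paediatrician services, the pilot is the place to find out whether referral and appointment status can be collected from parents. This is a matter of what data are gathered, so a statistical analysis plan cannot supply it later.

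**Working it through.** The protocol states no safety figure and no power calculation, so there is nothing to reproduce. The check has two parts.

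**What is collected, and from whom** (Table 1, Table 3, sections 4.5, 7.3 and 8.1)

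- Perceived harms: interview; Website arm only; optional.
- Child behaviour and impact (SDQ), parent distress (DASS-21): survey; both arms; baseline and 4 months. Section 11.1 plans between-arm estimates with 95% confidence intervals.
- Health service use: survey; both arms. Table 1 summarises it as services used, number of times, distance and out-of-pocket cost.
- Clinic database: both arms, but listed only for recruitment counts.
- SAEs: reportable in either arm, but no scheduled question asks about them.
- Waitlist or appointment status: not listed in either arm.

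A paediatrician visit may well appear under service use. The absence of one is ambiguous. Section 4.2 admits both accepted and declined referrals, so a family with no visit at 4 months could be (i) still waiting, (ii) declined by the clinic or (iii) withdrawn from the waitlist. Only (iii) is the event in section 2.3.1, and nothing listed separates the three.

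**What the numbers could show**

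*Interview alone.* Section 4.2 wants about 20 interviewees; the ceiling is the 30 in the arm. If none of n reports a harm, the one-sided 95% upper limit is 1 − 0.05^(1/n):

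- n = 20: 13.9%
- n = 30: 9.5%

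The chance that a harm with true rate p goes entirely unseen is (1 − p)^n. With n = 20 this is 0.90^20 = 12% for a 10% harm and 0.95^20 = 36% for a 5% harm. These figures treat interviewees as a random sample, which volunteers are not, and they mainly reflect the small number.

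*After the fix.* If exit were recorded in both arms with 30 per arm, the 95% half-width for the difference would be 1.96 × √[p₁(1 − p₁)/30 + p₂(1 − p₂)/30]. The documents give no background exit rate, so control exit p₁ is assumed at 5% to 20%, with Website exit p₂ higher by 10 to 30 points:

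- 5% v 15%: 1.96 × √[(0.0475 + 0.1275)/30] = 15.0 points
- 10% v 20%: 1.96 × √[(0.09 + 0.16)/30] = 17.9 points
- 20% v 30%: 1.96 × √[(0.16 + 0.21)/30] = 21.8 points
- 20% v 50%: 1.96 × √[(0.16 + 0.25)/30] = 22.9 points

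Power for a 10-point increase would be about 25% (5% v 15%), 19% (10% v 20%) and 14% (20% v 30%). All of this assumes that 30 per arm hold a waitlist place and respond. With m per arm instead, the half-width grows by √(30/m).

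**The case against.** The strongest reply is that this is a low-risk feasibility pilot built on publicly available strategies, that it promises no formal safety conclusion, and that it does hold controlled information on harm. Much of that stands.

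- A reader might infer that the pilot yields no safety information. It does: the SDQ, its impact supplement and the DASS-21 are compared between arms and can show average worsening. SAEs are reportable in both arms, and parents have a research phone and email.
- A reader might infer that only contented volunteers are heard. Website parents are contacted by SMS about the interview, and those who withdraw are specifically invited.
- A reader might treat leaving the waitlist as plain harm. Section 2.3.1 calls the risk theoretical and allows that attrition may be benign; section 2.2 counts it as a possible gain.
- A reader might infer that use of paediatricians is not measured at all. The service-use question is only summarised in Table 1 and may capture visits. What is missing is why a family had none.
- A reader might infer that section 8.1 excludes serious events in the child. The consented participant is the parent, but the eligibility lists attach child attributes to the participant, section 8 deals separately with child deterioration and welfare, and the HREC policy cited is not at hand. Coverage is unclear, not excluded.
- The binomial limits are largely a matter of small n, and the fix would not give a powered comparison.

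None of this supplies a control-arm question on perceived harms or a record of waitlist status in either arm.

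**Conclusion.** The point holds in limited form. The pilot cannot compare parent-perceived harms or waitlist exit between arms, and it does not pilot a measure of waitlist exit for the full RCT. The documents do not support the broader statement that no safety conclusion of any kind is possible.

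This is an inexpensive improvement, not a defect that undermines the primary objective. Its value is descriptive: an exit difference known to within about 15 to 23 points, given 30 per arm and the assumed exit rates, together with evidence on whether parents can report their status.

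The SAE wording is secondary. A clock that starts at occurrence cannot be met for an event first learned of at the 4-month contact, subject to whatever the HREC policy provides.

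**What to change.** Add to the existing 4-month survey, in both arms:

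1. Paediatrician referral and appointment status: accepted or declined; seen; still waiting; cancelled or left the waitlist, with the reason.
2. One brief question on any harm or serious event in the parent or the child.

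Report both by arm with confidence intervals, as description only. Show declined referrals separately, since they have no place on that clinic's waitlist to leave. Keep the interview to explain what the survey finds.

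In section 8.1, consistent with the HREC policy it cites, state whether SAEs in the index child are covered, and run the reporting clock from when the team becomes aware.

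The cost is a slightly longer survey and a short HREC amendment. The items should be in place before 4-month follow-up starts, because the information is hard to recover afterwards.

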**Summary of the validated measures.**

Strengths and Difficulties Questionnaire

The SDQ^17^ is a brief psychological assessment tool developed for 2-17 year old children and adolescents which consists of 25 items on psychological attributes. The SDQ has been well validated^18^ and is consistent over time in an Australian context^19^.

Strengths and difficulties Questionnaires with impact statement

This extended version of the SDQ asks additional information about the duration, level of distress, level of impairment, and the degree of burden their behaviour or emotions has on others, including their family.^20^

Depression, Anxiety and Stress Scale

The DASS-21 is a 21 question survey for adults, that measures emotions of depression, anxiety and stress. The DASS-21 has also been validated and there are accompanying norms for the Australian population.^21,22^a

# TRIAL DESIGN

# Overall design

A pilot randomised controlled trial will be implemented to assess the acceptability and feasibility of the FindWays website and compared trends in child and parent related outcomes, compared to a standard care control group,

*Design:* Pilot RCT comparing the FindWay website intervention group with a control group.

*Intervention*: FindWays website is a co-designed online service navigation platform and website providing evidence-based parenting strategies. Informed by qualitative study (HREC 2019.160) and co-design workshops, the website provides content on children’s behavioural and emotional problems. Specifically, this content includes strategies to help specific behaviour or emotional problems, describes providers and programs that can help child behavioural or emotional problems, and a list of local community services and individual professionals who can see children with a mental health care plan. Parents will have access to the intervention for 4 months.

*Control*: A standard care control group was chosen to measure the realities of trying to access paediatric help for the child’s behavioural or emotional problem. This also allows us to compare trends in efficacy of secondary outcomes between the two groups.

*Sample size:* There are no published data on the optimal size of a pilot RCT to assess acceptability and feasibility. However, prior studies conducted by this team have included between 15-30 participants in each trial arm, and the Melbourne Children’s Trial Centre has suggested a minimum of 20 participants. As such, I will aim to recruit 60 parents, with 30 in each arm.

*Setting:*Three specialist general paediatric outpatient clinics in Geelong, Victoria. There are no public paediatric outpatient clinics available to Geelong children, unless the family identifies as ATSI or migrant background. There are three private clinics available in Geelong, of which bulk billing is paediatrician dependent on a case-by-case basis.

# Trial population

The trial population will be all eligible parents of children, aged two-12 years. with a behavioural and/or emotional problem, who are referred to a paediatric clinic for their first review. These paediatric clinics will be either Geelong Children’s Clinic, Geelong Paediatric Group or Barwon Paediatrics. The referred child can either be accepted or declined by the clinic.

We expect to recruit at least 20 parents every month for three months. This estimate is based on the high number of monthly referrals for behavioural or emotional problems in 2-12 year old to these clinics (estimated to be 20 referrals every week across the 3 clinics). Further, the number of accepted referrals who were recruited within [name]’s qualitative study (HREC 2019.160), was 5 parents per week at each study site.

No power calculation has been done as the trial is not intended to assess the effectiveness of the intervention. Typically, acceptability and feasibility trials recruit around 20 participants, though 60 will give us a stronger indication of difference in acceptability between the intervention groups, and a larger number of eligible participants for the qualitative component of the study, which ideally requires around 20 participants to reach data saturation.

Exclusion criteria are listed in the table below. These criteria are justified because: i) children with a diagnosed intellectual disability or autism spectrum disorder require specialised treatments that are not listed within the platform; ii) children in out of home care are especially vulnerable and again require specialised programs with an emphasis on attachment and trauma; iii) any child requiring an urgent review (eg high severity or possibility of medical cause) is less likely to gain benefit from the website due to the shorter time frame waiting for a paediatrician review, and may be less likely to benefit from the programs and interventions listed in the website because of the increased severity.

Parents are the sole focus of the intervention, and the only source of outcome data. Children are not directed to use the website or participate in the collection of any measures. Only one parent will be consented for each child referred to the clinic.

**Table 2**. Inclusion and exclusion criteria

| *Inclusion criteria* | *Exclusion criteria* |
| --- | --- |
| Parent of child aged 2-12yo  BEP listed as primary concern on the GP referral letter for first appointment, i.e.:   - anxiety (eg excessive stress, worry), - behavioural problems (eg disruptive, defiant, hyperactive) - mood problems (eg depressed, emotional dysregulation) | Child in out of home care  Parent reported child intellectual disability or previously diagnosed ASD  Paediatrician defined need for an early review (eg to exclude medical problems) |

